## 10 CANCELTION AND COMPLETION

### 10.1 CANCELTION OF PARTICIPATION IN THE TRIAL

If the subject fails to comply with all study schedules, including efficacy and safety assessments, as well as discontinues protocol treatment for the following reasons (1. to 3.), participation in this trial should be canceled. This situation is called “cancellation of participation in the trial”.

If the protocol treatment is canceled before it has actually started, no observations should be performed, and appropriate treatment should be given so that the subject is not disadvantaged in

normal practice.

1. When the subject withdraws consent to participate in the study.
2. When “disease, etc.” that may lead to death or death occurs.
3. In addition, when the investigator determines that the risk of participating in the trial outweighs the benefits.

Basis for setting

- 1: Set from an ethical point of view.
- 2 – 3: Established from the viewpoint of subject safety.

## 10.2 CANCELATION OF THE ENTIRE TRIAL

If the following situations (1. to 6.) occur and the investigator (CI or PI), Jichi Medical University Central Clinical Research Ethics Committee, or director of the implementing medical institution decides that the entire trial should be discontinued, the entire trial may be canceled. This situation is called “cancellation of the entire trial”.

1. When an unpredictable serious “disease etc.” occurs and there is concern about disadvantage to the subject (mother, fetus, infant).
2. When a critical violation/non-compliance with the law and related laws or study plan is found.
3. When a fact that impairs or may impair ethical validity or scientific rationality is obtained.
4. When a critical risk to the subject is identified.
5. When an opinion is given by the Jichi Medical University Central Clinical Research Ethics Committee.
6. When the Minister of Health, Labour and Welfare requests cancellation or makes a recommendation.

In the event of cancellation in the entire trial, the PI will report to the CIs of all the implementing medical institutes, Certified Clinical Research Review Board, and to the administrators of the implementing medical institutions. In addition, the PI will contact the subjects and inform them of the change in the study schedule. In the event of cancellation of the entire trial, the subject will promptly discontinue the protocol treatment, and the safety of the subject (mother and fetus) will be ensured in accordance with the discontinuation criteria in 6.2.6 Criteria for discontinuation of protocol treatment.

## 10.3 COMPLETION OF THE TRIAL

The day when all the following six items (1. to 6.) are completed and the completion of this trial is announced in the implementation plan is “completion of the trial”.

1. End of enrollment of subjects in the trial and end of observation period.
2. Preparation of general report and its summary.
3. Listening to the opinions of Certified Review Board.
4. Submission to the director of the implementing medical institution.
5. Submission to the Minister of Health, Labour and Welfare and publication of the outline of the general report.
6. Reporting to the director of the implementing medical institution.

## **11 ANTICIPATED BENEFITS AND DISADVANTAGES, AND METHODS TO MINIMIZE RISKS**

### **11.1 ANTICIPATED BENEFITS**

Participation in this study may prevent the development of BPD in children who receive treatment with EM or AZM under the ABPC)/SBT combination. This treatment uses ABPC/SBT instead of ABPC, which is expected to treat a wider range of bacteria, and the administration period has been increased from 7 to 14 days, which may cure bacterial infections that could not be cured in 7 days. Therefore, we believe that both the control and test groups can be expected to have an effect on BPD that could not be expected with conventional methods. This study may lead to the establishment of antimicrobial therapy for preterm water withdrawal during preterm labor in Japan.

### **11.2 ANTICIPATED DISADVANTAGES**

Because subjects will be randomly assigned to either the study or control group, they will not be able to choose their preferred treatment. Regardless of which group they are assigned to, they may experience side effects (e.g., diarrhea) from the antimicrobial agents administered. Vascular pain may occur while receiving Erythrocine for Intravenous Infusion or ZITHROMAC Intravenous use.

### **11.3 METHODS TO MINIMIZE RISKS**

Regardless of which group a patient is assigned to in this study, if “disease, etc.” attributable to those drugs occur, the patient will be individually considered for treatment, including withdrawal of medication or cancellation of participation in the trial. Venous blood sampling, electrocardiography, and radiographic imaging will be performed using the same techniques as those used in routine medical care, so there will be no increase in risk as a result of participation in the study. The volume of blood drawn from subjects in this study is 10 mL/treatment, which is a medically safe volume. The volume of blood drawn from the children in this study is also 1.0-1.5 mL/treatment, which is a medically acceptable volume. If the birth weight is less than 1000 g, blood tests will not be required.

## **12 ETHICAL MATTERS AND MATTERS REQUIRING CONSIDERATION**

### **12.1 COMPLIANCE WITH LAWS AND GUIDELINES**

This study falls under the category of specified clinical trial under the Clinical Research Act (Act No. 16 of 2017) because the study drug falls under off-label use. Therefore, this study will be conducted in compliance with the Clinical Research Act and in accordance with ethical principles based on the Declaration of Helsinki.

The materials required by law, including the study protocol and implementation plan, will be reviewed and approved by a Certified Clinical Research Review Board. Thereafter, the CI at each site will obtain permission from the administrator of the respective site, and the PI will complete

registration in jRCT before commencing the study. If there are any changes to these materials, etc., the same procedure will be followed before the changes are put into effect.

Each CI of this study will be required to register with CREDITS (<https://www.uhcta.com/uth/member/>) and take the "Ethics and Code of Conduct Course" and the "Conducting Clinical Research Course" from the e-learning program before the study begins. However, if the CI has already completed the "Required Courses for Principal Investigators" designated by the Ethics Committee of each institution within one year, the CI will be deemed competent to conduct the study by submitting a record of such course.

## 12.3 HANDLING OF PERSONAL INFORMATION, ETC.

### 12.3.1 ANONYMIZATION

Data containing personal information of subjects (mothers and fetuses) and children to be collected in this study will be transcribed to the electronic case report form without including personal information. The subject identification code (anonymization number) will be a combination of alphanumeric characters that do not have regularity with the medical record ID, and will be a common study code and an institution code with a three-digit alphanumeric case number. In addition, an anonymization correspondence table for identifying individual subjects will be created and stored.

The anonymization correspondence table will be held only by the institution that obtained the subject's consent.

In this study, the Jichi Medical University Central Clinical Research Ethics Committee and the person in charge of monitoring this study may directly inspect and review patients' medical records (e.g., medical charts), but this will be done with caution to avoid information leakage.

### 12.3.2 RIGHTS OF SUBJECTS AND OTHERS WITH RESPECT TO PERSONAL INFORMATION

Each CI will disclose personal information, notify the purpose of use, correct, add, delete, or suspend on personal information and personal identification codes (anonymization numbers) held in study at the request of subjects. However, if there is a justifiable reason for not responding to the request, such as when there is a risk of harm to the rights of the medical institution, the proper conduct of clinical study, or the rights of the subject him/herself, the reason will be explained to the subject, etc.

**12.4 COMPENSATION FOR HEALTH HAZARDS**

If the subject (mother) suffers health problems, appropriate treatment will be provided within the scope of insurance coverage. The subject shall bear the co-payment of medical expenses. Since this study is an off-label use of an already-approved drug, the subject will be covered by clinical research insurance to compensate for any health damage. In the event of a health hazard for which a causal relationship with this study cannot be denied, compensation will be provided according to the extent of the health hazard and the terms of the clinical research insurance policy. However, if the subject is negligent, the subject will not be covered. If the physician is at fault, compensation will be provided through the physician liability insurance. The clinical research insurance policy shall be concluded promptly after the initial approval is obtained.

**12.5 METHOD OF TREATMENT IF NOT PARTICIPATING IN THE STUDY**

If not participating in the study, antimicrobial therapy (penicillin or cephem antibiotics or combination erythromycin) will be administered at each practicing institution. The best treatment appropriate for the subject will be selected even if the subject does not participate in the study.

**12.6 PROVISION OF MEDICAL CARE AFTER COMPLETION OF THE STUDY**

After termination of pregnancy or completion of protocol treatment, the best treatment for intrauterine infection will be provided within the scope of insurance coverage and in accordance with the subject's wishes.

**12.7 HANDLING OF STUDY RESULTS ON GENETIC CHARACTERISTICS, ETC.**

Not applicable because this study does not involve any testing or analysis that would yield genetic characteristics of the subjects.

**12.8 SUBJECTS' FINANCIAL BURDEN, AND BURDEN REDUCTION EXPENSES**

The study drugs used in this study will be paid for by the research fund of this study, so there will be no financial burden on the subjects. All other costs will be paid by the subject's health insurance and the subject's co-payment. In addition, there is no difference in treatment between the subject and pregnant women with pPROM who do not participate in the study in terms of expenses that are not covered by insurance, such as meals and bed differentials, which are considered to be expensive.

Since the number of hospital visits and examinations is expected to increase as a result of participation in this study, the financial burden on subjects may also be greater than that of regular medical care. To reduce the burden on subjects, a 10,000 yen burden reduction fee will be paid only once during the study period. The burden reduction fee will be explained in advance in the consent document, and the fee will be transferred to the account designated by the subject after participation in the study. Whenever possible, subjects are requested to fill out information on a form indicating

the account number, etc., before leaving the hospital, place the form in a self-addressed envelope, and send it to the Coordinating Office. The Jichi Medical University Accounting Section will bear the transfer fee. The account number and other information will not be used for any purpose other than the payment of burden reduction expenses.

## **13 RESEARCH FUNDING, CONFLICTS OF INTEREST, AND DISCLOSURE OF INFORMATION**

### **13.1 SOURCES OF FUNDING FOR THIS STUDY**

This study is funded by the Japan Agency for Medical Research and Development, Research and Development Fund (Project for Baby and Infant in Research of health and Development to Adolescent and Young adult - BIRTHDAY) "Development of Prevention Method for BPD by Azithromycin Administration for Pregnant Women with pPROM at <28 Weeks of Gestation" (PI: [name]) and the research fund distributed to the PI from Jichi Medical University.

### **13.2 CONFLICTS OF INTEREST**

Conflicts of interest regarding the study as a whole and conflicts of interest of individual PI, CI, and SI shall be reported prior to the commencement of the study, and the fact shall be confirmed by the respective institutions to which the PI and SIs belong. Conflicts of interest related to the study as a whole and conflicts of interest of individuals shall be reported prior to the commencement of the study, and the fact shall be confirmed at each affiliated institution. If the medical institution has a committee that confirms and advises on the status of conflicts of interest, the fact shall be confirmed by the committee. If no committee has been established at the institution, the conflict of interest should be reported to the head of the study institution or the administrator of the implementing medical institution, and the fact should be confirmed by that person.

A conflict of interest management plan shall be formulated for each implementing medical institution with the results of fact-finding on the status of conflicts of interest, and conflicts of interest shall be managed and disclosed after obtaining approval from the Jichi Medical University Central Clinical Research Ethics Committee. The status of conflicts of interest shall be disclosed in the same manner when the study results are published. The status of conflicts of interest shall also be disclosed to study subjects.

Appropriate re-declaration and approval will be obtained after the commencement of study. For example, when there is a change in the status of conflicts of interest, when adding or changing the CI or SIs, when making periodic reports, or at other appropriate times, the status of conflicts of interest and conflict of interest management plan, etc. should be reviewed, re-declared, and again approved by the Jichi Medical University Central Clinical Research Ethics Committee.

### **13.3 METHOD OF INFORMATION DISCLOSURE**

The study summary and results of this study will be registered in the publication system for clinical trial plan and study summary (JRCT: <https://jrct.niph.go.jp/>) maintained by the Ministry of Health, Labour and Welfare, and will be made public in JRCT by submitting the clinical trial plan to the Minister of Health, Labour and Welfare. If there are any changes in the content, the JRCT

should be revised, and the changes should be notified to the Minister of Health, Labour and Welfare after obtaining the approval of the Jichi Medical University Central Clinical Research Ethics Committee. In addition, the information should be updated at least every year in accordance with the law.

### 13.4 PUBLICATION OF RESULTS

The results of the study will be made public through paper submission and conference presentations. In addition, an outline of the summary report and the results regarding the primary outcome will be notified to the Minister of Health, Labour and Welfare and published in jRCT. The outline of the summary report will be submitted to the Minister of Health, Labour and Welfare around March 2025, within one year after the end of the observation period when all collection periods are completed. However, the publication in the jRCT will be made within 2025 after the publication of the article. The first author of a manuscript submitted to a journal should be the CI or SI from the institution with the highest number of registered cases at the end of the study enrollment. The second author should be the CI or SI from the institution with the next highest number of registered cases. Up to two obstetricians and two neonatologists from each institution will be considered as authors. The order of authors after the third author shall be the order of the institution with the largest number of enrolled patients. [name], and [name], who contributed to the protocol development for this study, will be the authors. [name], the PI, and [name] will be co-corresponding authors. For facilities that did not enroll any cases during the enrollment period, their names will be listed in the Acknowledgement.

For the main article on the detection of *Ureaplasma* spp. and *Mycoplasma* spp. the PI, [name], and the CI, [name], will be the corresponding authors. The CI at each institution shall be the authors (the order shall be alphabetical by last name). [name] shall be the last author. In addition, any researcher who has been involved in this study at the Department of Developmental Medicine, Research Institute, Osaka Women's and Children's Hospital may be an author. The first author shall be determined by [name].

PI who participated in this study may perform secondary analyses using the data obtained. However, approval from the PI is required to perform secondary analyses. The paper should include the PI and CIs (at least one or more) who participated in this study. CI at each site other than the authors and [name], [name], who contributed to the protocol development, should be listed in the acknowledgments. Investigators involved in the secondary analysis may be considered authors even if they were not involved in this study. The investigator who submitted the secondary analysis will be the corresponding author and will determine the first author.

## 14 STATISTICS

### 14.1 POPULATION ANALYZED

The analysis target population is as follows: The analysis population for the primary outcome will be the "Full Analysis Set".

#### 1. Full Analysis Set (FAS)

Subject population (mother, fetus/infant) excluding those who fall under the following from all randomized subjects

- Subjects who have never received protocol treatment
- Subjects who received protocol treatment at least once, but data were not obtained after the treatment
- Subjects who do not meet the eligibility criteria

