## 5.2 TARGET NUMBER OF CASES

### 5.2.1 TARGET NUMBER OF CASES

Target number of cases: 50 in the test group and 50 in the control group (total 100 cases)

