### 5.2.2 REASONS FOR SETTING THE NUMBER OF CASES

In this study, since fetal and neonatal deaths were considered to be at higher risk of developing BPD and infant deaths up to 36 weeks PMA were also considered as one of events, infant deaths up to 36 weeks PMA (5%) were also taken into account to establish effect sizes for the two groups.

In a previous foreign study, the incidence of BPD36 was 26.4% (29/110, all children survived) when 110 pregnant women who developed pPROM at <28 weeks of gestation were treated with AZM. In a previous study in Japan, the incidence of BPD36 was 18.2% (2/11, all children survived) when 11 pregnant women with pPROM at <28 weeks of gestation were treated with ABPC/SBT + AZM. In addition, when ABPC/SBT + AZM was administered to 10 pregnant women with pPROM at <28 weeks of gestation from June 2013 to May 2020 at Saga Hospital, the incidence of BPD36 was 40.0% (4/10, all children survived) ([name] *et al*, unpublished data). Based on the above, the incidence of moderate or severe BPD36 or child death by 36 weeks PMA in the intervention group (AZM group) was assumed to be 18.0% to 40.0%.

On the other hand, the literature search did not retrieve any reports of EM administration to pregnant women with pPROM at <28 weeks' gestation alone. Therefore, we assumed that the incidence rate of moderate or severe BPD36 or infant death by 36 weeks PMA in the control group (EM group) was 60.0% based on the general BPD36 incidence rate.

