The median number of weeks of gestational duration for pregnant women with pPROM is 2 weeks. Based on the annual number of deliveries, the number of births by week, and the percentage of pPROM, we can estimate that 1,200 newborns per year are born at <30 weeks to pregnant women with pPROM complications. In the 20 regional and comprehensive perinatal centers scheduled to participate in this study, the number of cases is estimated to be approximately 200 per year over a 2-year period. Assuming that 50% of the patients meet the eligibility criteria for this study and consent is obtained, 100 patients can be enrolled over a two-year period, and from the viewpoint of feasibility, the target number of cases for this study was set at 100. Under a two-tailed test and a significance level of 5%, the power of detection ranged from 0.516 to 0.995 when the assumed BPD36 incidence rate in the intervention group was 18.0% to 40.0%, which is considered to guarantee a power of at least 0.5.

For reference, the power curve for the BPD36 incidence rates of 18.0% to 60.0% in the intervention group are shown below. In addition, the incidence rates in previous foreign and domestic studies and the study at Saga Hospital are indicated by red lines.

[figure not shown]

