## 14.2.2 ANALYSIS OF PRIMARY OUTCOME

| Background information/primary outcome/secondary outcomes                                                             | FAS/PPS                      | Statistics                                                                                                                                                                                                                                                                                                                                                                                         |
|-----------------------------------------------------------------------------------------------------------------------|------------------------------|----------------------------------------------------------------------------------------------------------------------------------------------------------------------------------------------------------------------------------------------------------------------------------------------------------------------------------------------------------------------------------------------------|
| Primary outcome
Incidence rate of either moderate/severe BPD 36 or IUFD at or less than 36 weeks 0 days | Mainly FAS, followed by PPS. | Intervention group vs. control group
(1) The difference in crude rate, 95% CI. (2) adjusted risk difference and 95% CI by the Mantel-Haenszel method, adjusted for gestational weeks at onset of pPROM (22 weeks 0 days to 23 weeks 6 days, 24 weeks 0 days to 27 weeks 6 days) and institute (institute where early caffeine will be used, institute where early caffeine will not be used)**. |

In analyses using FAS, all subjects with missing primary outcome will be treated as having "moderate or greater BPD36 or occurrence of death in child up to 36 weeks PMA" for any reason. In analyses using the PPS, subjects with missing primary endpoints will be excluded from the analysis.

A two-tailed test will be conducted with the null hypothesis that "the proportion of moderate or higher BPD36 or child deaths up to 36 weeks PMA is equal between groups" and the alternative hypothesis that "the proportion of moderate or higher BPD36 or child deaths up to 36 weeks PMA is different between groups." The p-value will be calculated by testing the difference in proportions. The significance level is set at 0.05.

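### The primary analysis set removes randomised women after the arm is known, and undosed women are not followed, so the open-label comparison is exposed to arm-dependent exclusion

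*Protocol*

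**What the plan says.** Section 14.1 makes the FAS the population for the primary outcome. It starts from all randomised subjects and takes out three groups:

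- "Subjects who have never received protocol treatment";
- "Subjects who received protocol treatment at least once, but data were not obtained after the treatment";
- subjects who fail the eligibility criteria. This exclusion is not limited to facts known before randomisation and carries no requirement for blinded review.

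Section 14.2.2 then handles missing data: "In analyses using FAS, all subjects with missing primary outcome will be treated as having" an event, whatever the reason. In the per-protocol set such subjects are excluded instead.

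On follow-up, section 10.1 states: "If the protocol treatment is canceled before it has actually started, no observations should be performed". By contrast, section 6.2.6 keeps women who stop treatment after starting it in the study and on the observation schedule.

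On timing and blinding, the design is open-label and only the committee judging BPD is blinded (1.1, 16.6). REDCap displays the assigned group at enrolment (7.4). Randomisation may fall up to 3 days after consent and the first dose up to 4 days after consent (4.1). The schedule puts registration on Day 0 and the first dose on Day 1 (Table 1.3-1).

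**The concern.** Randomisation protects a comparison only if membership of the analysis set cannot depend on the arm. Leaving out undosed subjects is usually harmless when nobody knows the allocation. Here the physician and the woman know it before the first infusion.

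The protocol itself supplies grounds for different behaviour by arm. It reports EM as ineffective against *Ureaplasma* because of low intrauterine transfer (2.1.3) and says its use with ABPC/SBT is rare in Japan (2.2). The EM regimen also needs more administrations per day (6.2.1). Four exclusion criteria (5.1.2, items 6, 7, 17 and 18) rest on the attending physician's opinion and could be judged afresh once the arm is known.

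The comparison informs whether a phase III trial follows (2.2) and supplies its sample-size inputs (2.1.3). A distortion would carry forward, and outcomes that were never collected cannot be restored by a later analysis plan.

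**Working it through.** **Step 1: the plan's power figure.** Inputs from 5.2.1 and 5.2.2: 50 per arm, two-sided 5%, EM event rate 0.60, AZM event rate 0.18 to 0.40. With the pooled-variance normal approximation,

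power = Φ[(|p₁ − p₂| − 1.96·SE₀)/SE₁], SE₀ = √(2p̄(1 − p̄)/n), SE₁ = √(p₁(1 − p₁)/n + p₂(1 − p₂)/n).

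- 0.60 vs 0.40: SE₀ = 0.1000, SE₁ = 0.0980, argument 0.041, power 0.516.
- 0.60 vs 0.18: SE₀ = 0.0975, SE₁ = 0.0880, argument 2.60, power 0.995.

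Both match the protocol ("Under a two-tailed test and a significance level of 5%, the power of detection ranged from 0.516 to 0.995"). The calculation uses all 100 women, with none excluded and none missing.

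**Step 2: where each randomised woman ends up.**

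| Woman | In the FAS? | Outcome collected? | Counted as |
|---|---|---|---|
| Treatment cancelled before first dose | No (14.1) | No (10.1) | Dropped |
| Dosed, no data afterwards | No (14.1) | No | Dropped |
| Dosed, some later data, primary outcome missing | Yes | No | Event (14.2.2) |
| Dosed, later stops treatment, followed | Yes | Yes (6.2.6) | As observed |
| Judged ineligible after randomisation | No (14.1) | Not stated | Dropped |

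The second and third rows differ only in how soon contact was lost, yet they are handled in opposite ways. The third row assumes that the exclusion refers to the absence of any data at all. If it means primary-outcome data, the third row moves into the second, and the missing-equals-event rule has no dosed women left to act on.

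**Step 3: how few exclusions matter.** Suppose the full randomised result falls at the design rates, EM 30/50 and AZM 20/50. The test is z = d/√(p̄(1 − p̄)(1/n₁ + 1/n₂)). Now drop from one arm two women without data who would have counted as events had they been kept.

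| Data set | Difference (95% CI) | z | p |
|---|---|---|---|
| All randomised: 30/50 vs 20/50 | 20.0 points (0.8 to 39.2) | 2.00 | 0.046 |
| Two dropped from EM: 28/48 vs 20/50 | 18.3 points (−1.1 to 37.8) | 1.81 | 0.070 |
| Two dropped from AZM: 30/50 vs 18/48 | 22.5 points (3.2 to 41.8) | 2.23 | 0.026 |
| Two dropped from each: 28/48 vs 18/48 | 20.8 points (1.3 to 40.4) | 2.04 | 0.041 |

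One-sided exclusion moves the result across 0.05. Balanced exclusion barely moves it. The issue is therefore imbalance between the arms, not the number lost.

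**The case against.** **A reader might infer that 14.1 and 14.2.2 contradict each other.** They do not, strictly. The missing-data rule is worded for analyses in the FAS, and 14.1 first decides who is in it. The rules can run in sequence, and no subject is both removed and counted as a failure. What stands is the inconsistency in Step 2. The key phrase is not defined in the protocol, although an analysis plan not at hand may define it.

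**A reader might infer that women who deliver between allocation and first dose bias the result because they are at high risk.** They have not yet received the allocated macrolide, and only ABPC or ABPC/SBT is allowed in that interval (6.2.1, 6.4.2). Their numbers should balance in expectation. Leaving them out changes the population studied, but bias requires an arm-dependent decision.

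**A reader might infer that many women would be lost.** With the 2-week median in 5.2.2 and an assumed constant hazard, 1 − 0.5^(1/14) = 4.8% deliver within one day and 1 − 0.5^(3/14) = 13.8% within three. The planned gap is one day, so the lower figure is the apter one. Even that applies a median for women with pPROM generally to a trial that excludes those whose pregnancy is likely to be ended imminently.

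**A reader might infer that the exclusions should go because they cost power.** At 40% vs 60%, dropping 10% per arm leaves 45 and power 0.475. Suppose instead that all 50 are kept and 10% of AZM women are undosed with the control rate. The AZM rate becomes 0.9 × 0.40 + 0.1 × 0.60 = 0.42 and power is 0.436. Power does not favour the change.

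**Other points against.** Both arms receive the same ABPC/SBT and an active macrolide on the same intravenous and oral days, and vascular pain is listed for both (11.2), which limits the motive to treat the arms differently. Hospital charts would still exist for undosed women. The trial is an exploratory phase II, and the protocol never calls the FAS intention-to-treat. These points limit the likely size of any bias. They do not remove the route to it, and charts help only if the protocol permits their use.

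**Conclusion.** The concern holds. A stated rule lets randomised women leave the primary comparison after their arm is known, through three routes: not starting treatment, having no data after starting, and being judged ineligible later. For the first route the protocol also stops the data collection needed to check the effect. The no-later-data exclusion is inconsistent with the missing-equals-event rule without being a strict contradiction.

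The size of any bias cannot be computed, because the protocol gives no expected exclusion rate by arm or overall. The shift from p = 0.046 to 0.070 or 0.026 is an illustration. It assumes a result exactly at the 60% and 40% design rates, two women lost from one arm only, and that both would have counted as events. It shows sensitivity and does not predict a bias. The finding rests on the open-label design and the visible allocation; it does not rest on lost power or on a particular proportion of early deliveries.

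**What to change.** 1. In 14.1, define the primary set as all randomised women with their fetus or infant, analysed as allocated, and apply missing-equals-event to all of them.
2. Delete the never-dosed and no-later-data exclusions. Allow exclusion only for withdrawal of consent to data use, and for ineligibility documented from facts that predate randomisation and judged without knowledge of the arm.
3. In 10.1, limit the no-observation rule to women not yet randomised. For every randomised infant whose mother has not withdrawn consent, collect delivery, vital status and BPD36 data. Without this step, undosed women would enter the primary analysis only as imputed events. The care these women receive is not affected.
4. Keep the present FAS as a sensitivity set.

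The cost is a change of wording and chart data for what should be a small number of women. The downside is some dilution of the effect and a small loss of power from including undosed women (0.436 against 0.475 in the 10% example above).
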